## Methods

### Pre-intervention – wound bed preparation

To optimise the quality of the wound bed prior to administration of autologous spray-on skin, wound bed preparation will be standardised; all patients identified for inclusion into the trial will be receive the same pre-intervention protocol before randomisation. For wounds > 1 cm deep, negative pressure dressings will be applied with a Prontosan® [B. Braun] soak at each change. For wounds < 1 cm deep, IntraSite conformable [Smith & Nephew] (with Prontosan® soak as above) will be used.

On the day of randomisation, the index wound will be further cleansed via ultrasonic debridement to remove as much biofilm and devitalised tissue as possible. This will allow for uniformity in wound base appearance prior to randomisation. After ultrasonic debridement, wounds will be swabbed and the swabs stored for future microbiome analysis.

### Intervention – spray on skin

Through a series of validated steps, ReCell® [Avita Medical] enables disaggregation of cells from a patient’s skin and the preparation of a suspension of these cells that can be sprayed or dropped directly onto the prepared wound bed.

The skin from which the suspension is prepared comes from a small split skin graft (SSG) collected from the patients’ upper thigh. An electric dermatome set at 2 mm depth or a scalpel blade (size 10) placed at a shallow angle will be used to harvest the skin. In comparison with traditional SSG, the size of the sample for the spray on skin preparation is much smaller and will be approximately 2cm^2^. The harvest site area will be recorded to control for the dose of skin cells applied as a possible co-variate in statistical analyses.

A small amount of the harvested skin preparation will be reapplied to the harvest site to enable more rapid healing. The harvest site will be dressed with Surfasoft® [Tauren] and Mepilex® Border [Mölnlycke].

The process of disaggregating the cells is performed with ReCell® [Avita Medical] as previously described in [20] and relies on the enzyme trypsin to allow the epidermis to be separated from the dermis. The cells at the epidermal-dermal junction can then be scraped off using a scalpel and are collected and filtered before being dropped or sprayed onto the wound site. Immediately after autologous skin application the index wound will be dressed with Surfasoft® dressing for a minimum of 5 days. Secondary absorbent dressings may be changed as required without disturbing the Surfasoft® layer during this time to allow adequate cell adherence.

Patients randomised into the control arm will continue with standard wound care procedures as per normal day to day proceedings of the hospital Outpatients clinic following ultrasonic debridement.

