### Adverse events

Although it is expected that the intervention will be safe, adverse events (AE) will be pre-specified and reported to the Data Safety and Monitoring Board (DSMB; see below) in accordance with NHMRC position statement of monitoring and reporting of clinical trials. A DSMB will be established that includes an independent researcher and two independent clinicians including one with experience in clinical trials and the other with managing diabetic foot infections. As this is not a systemic intervention, there will be no stopping rules based on any haematological or biochemical parameters.

A severe adverse event (SAE) form will be reported promptly to the DSMB if any of the following occurs:
Death from any causeMajor limb amputation of the same leg as the index ulcer at any stage up to 12 months from enrolmentMajor infection of the harvest site as defined as the requirement for admission to hospital, surgical debridement or intravenous antibiotics

An AE form will be reported if any of the following occurs:
Readmission for any reason related to infection or deterioration of the index ulcerMinor amputation unrelated to the index ulcer, but on the same foot as the index ulcer (after enrolment)Minor infection of the harvest site as defined by erythema and the requirement for oral antibiotic therapy for thisDelayed healing of the harvest site as defined by persistent need for a dressing on the harvest site at or beyond the 4 week visit

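### The 2 mm dermatome setting does not fit the split skin graft that the same paragraph describes, and the two must be reconciled

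*Protocol article*

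**What the plan says.** All the harvest details are in the protocol article, Methods, under Intervention – spray on skin.

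- **Donor tissue:** the skin for the cell suspension "comes from a small split skin graft (SSG) collected from the patients’ upper thigh".
- **Size:** compared with a conventional graft, the sample is "much smaller and will be approximately 2cm^2".
- **Tool and depth:** "An electric dermatome set at 2 mm depth or a scalpel blade (size 10) placed at a shallow angle". The 2 mm setting appears once, and no depth is given for the scalpel.
- **Processing:** the method "relies on the enzyme trypsin to allow the epidermis to be separated from the dermis". It continues: "The cells at the epidermal-dermal junction can then be scraped off using a scalpel".
- **Control arm:** standard wound care continues after ultrasonic debridement. No harvest is described.

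The Adverse events section makes three harvest-site events reportable. Major infection goes on the severe adverse event form. Minor infection and delayed healing go on the adverse event form, with delayed healing defined as "persistent need for a dressing on the harvest site at or beyond the 4 week visit".

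**The concern.** A split graft, by the meaning of the term, takes part of the skin thickness and leaves some dermis at the donor site. The neighbouring statements point the same way: a scalpel held at a shallow angle is offered as an interchangeable tool, and the cells collected lie at the epidermal-dermal junction. The delayed-healing definition implies that a donor site is expected to be free of dressings by about four weeks. Against this, the one depth printed is 2 mm, which looks too deep for the procedure described.

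What is at stake is donor-site safety. The harvest is made only in the spray-on arm, in people with diabetes, and the events that a deeper wound might increase are those the protocol has chosen to monitor.

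**Working it through.** **Can the figure be reproduced?** No. The 2 mm is a device setting with no inputs in the article, so it can only be compared with the description around it and with assumed thicknesses.

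**Inputs from the article:** depth 2 mm; split skin graft, upper thigh; two alternative tools; total recruitment 150 in two arms.

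**Inputs assumed (the article gives neither):** split-graft thickness 0.15 to 0.75 mm; thigh skin thickness (epidermis plus dermis) 1.0 to 3.0 mm.

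**Step 1. The setting against an assumed split-graft thickness.** Ratio = 2 mm / graft thickness.

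| Assumed graft thickness (mm) | Ratio |
|---|---|
| 0.15 | 2 / 0.15 = 13.3 |
| 0.30 | 2 / 0.30 = 6.7 |
| 0.45 | 2 / 0.45 = 4.4 |
| 0.75 | 2 / 0.75 = 2.7 |

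The setting exceeds the graft thickness throughout the assumed range.

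**Step 2. The setting against an assumed skin thickness.** Fraction removed = min(1, 2 mm / skin thickness).

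| Assumed skin thickness (mm) | Fraction removed | Wound |
|---|---|---|
| 1.0 | 100% | full thickness |
| 1.5 | 100% | full thickness |
| 2.0 | 100% | full thickness |
| 2.5 | 2 / 2.5 = 80% | partial |
| 3.0 | 2 / 3.0 = 67% | partial |

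A full-thickness wound follows at 2 mm or less and not above it.

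**Step 3. Participants who could be affected.** With equal arms, 150 / 2 = 75 are in the spray-on arm. The article does not say how many would be harvested by dermatome rather than scalpel, so 75 is a ceiling.

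**Step 4. Effect on the trial's statistics.** The sample size rests on healing proportions of 45% and 70%, 80% power and a 5% significance level. Harvest depth enters none of these, nor the definition or primary analysis of index-ulcer healing.

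**The case against.** The strongest reply is that the article contains no second figure that conflicts with 2 mm. Without a stated skin, graft or scalpel depth, the mismatch is between a number and a term, and its size comes from outside assumptions. That stands. So does the point that the neighbouring statements carry less weight than the word split: a shallow angle is not a depth, and the trypsin step shows that the harvested sample contains dermis but not how much is left behind.

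Several stronger readings are tempting, and the article does not support them:

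- *A reader might infer that the setting necessarily makes a full-thickness wound.* It does so only where skin is 2 mm thick or less. At 2.5 mm and 3.0 mm, 20% and 33% of the thickness would remain.
- *A reader might infer that about 75 people are exposed.* The scalpel is allowed, so that number is an upper bound.
- *A reader might infer that sites have no other depth instruction and have harvested at 2 mm.* This is a condensed article that cites a previously described process. The full protocol and device instructions are not shown, and a misprint here does not establish what was done.
- *A reader might infer that the cells delivered differ by depth or tool, or that costs rise in the spray-on arm.* The article records harvest area as the possible dose covariate and does not link depth to cell yield. It gives no figures from which a cost effect could be estimated.

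It is also fair to say that any donor wound falls in one arm by design, and that harvest-site harm is monitored. Monitoring would detect an excess of events, but it does not make the printed setting fit the procedure.

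**Conclusion.** The point holds as an internal mismatch: a stated operating setting does not fit the procedure it belongs to. It is not a complaint about detail left out of a condensed article, because the setting is printed.

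The comparison with graft thickness carries the conclusion: at 2.7 to 13 times the assumed range, no value in that range accommodates 2 mm. The comparison with skin thickness shows how serious the result could be (67% to 100% removed) but does not settle that the wound would be full thickness. Both ranges are assumptions. On them, a unit or decimal error is probable but not proven, and the article cannot show which statement is wrong.

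If the setting were followed, the consequence would be a deeper donor wound in at most about 75 participants, with a possible rise in harvest-site infection and delayed healing. The size of that rise cannot be estimated from the article. The mismatch merits correction on safety grounds, not because it threatens the primary comparison.

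**What to change.** Check the 2 mm setting, the split skin graft description and the shallow-angle scalpel alternative against the full protocol and the device instructions, and correct whichever statement is wrong. The discussion shows that recruitment has begun and that a second hospital has been added, so ask both sites which dermatome setting has actually been used. The correct setting is for the sponsor to confirm from those sources; none is suggested here.

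The cost is one corrected statement and a query to two sites. The sample size and analysis do not change.

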### Follow up measurements

Patients will be followed up at predefined time points. This will coincide with routine outpatient visits ordinarily scheduled at 4, 10, 18, 26, 39 and 52 weeks from randomisation with phone consultations every fortnight to determine total ‘ulcer-free’ days following healing. At each scheduled visit, the wound will be assessed in terms of location (exact; forefoot vs. hind- and mid-foot), depth, dimensions, wound volume and wound area (as measured by Silhouette™ [Aranz Medical]), wound quality (patchy vs. confluent, % epithelialisation), probe to bone test and photography. Both feet will be assessed for new wounds. Blood tests will be (lipids, C-reactive protein, full blood examination and renal and liver function tests) will be performed as clinically indicated, but an HbA_1c_ will be measured at 3, 6 and 12 months to determine the change from recruitment. All patients will receive standard care related to off-loading, ongoing diabetes management and infection management as per the usual management protocol of the multi-disciplinary foot ulcer teams. In addition to baseline, an EQ-5D-5 L [22] will be performed at 26 and 52 week visits to ascertain change in health-related quality of life [24]. The primary outcome will be assessed at the 26-week visit.

### Adverse events

Although it is expected that the intervention will be safe, adverse events (AE) will be pre-specified and reported to the Data Safety and Monitoring Board (DSMB; see below) in accordance with NHMRC position statement of monitoring and reporting of clinical trials. A DSMB will be established that includes an independent researcher and two independent clinicians including one with experience in clinical trials and the other with managing diabetic foot infections. As this is not a systemic intervention, there will be no stopping rules based on any haematological or biochemical parameters.

A severe adverse event (SAE) form will be reported promptly to the DSMB if any of the following occurs:
Death from any causeMajor limb amputation of the same leg as the index ulcer at any stage up to 12 months from enrolmentMajor infection of the harvest site as defined as the requirement for admission to hospital, surgical debridement or intravenous antibiotics

An AE form will be reported if any of the following occurs:
Readmission for any reason related to infection or deterioration of the index ulcerMinor amputation unrelated to the index ulcer, but on the same foot as the index ulcer (after enrolment)Minor infection of the harvest site as defined by erythema and the requirement for oral antibiotic therapy for thisDelayed healing of the harvest site as defined by persistent need for a dressing on the harvest site at or beyond the 4 week visit

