### Rationale

We hypothesise that the use of ‘spray-on’ autologous skin grafting (ReCell®; Avita Medical) in DFU will decrease healing time and thereby reduce overall cost of treatment. Autologous ‘spray on’ skin aids epithelial regeneration and has been used successfully in the treatment of scars and burns and other ulcers [19], particularly when traditional split skin grafting is not feasible. Although it has shown some early promise in a small case series of 4 ft ulcers [20] and for other chronic ulcers [19], no randomised trial of this product has been completed or is currently planned. The aim of this study is to assess the potential benefit of spray-on skin as a superior, and cost-effective, management strategy for DFU.

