### Secondary outcomes

Secondary outcomes include: i) index ulcer free days at 12 months, ii) time to full epithelialisation of the index ulcer, iii) trajectory of wound healing of the index ulcer (defined as volume and measured using Silhouette™), iv) major adverse events, v) any minor or major lower limb amputation, vi) all-cause mortality, vii) re-ulceration of the index ulcer, viii) the development of any new ulcers ix) total costs of inpatient and outpatient costs (see economic analysis, below), x) readmission to hospital and xi) health-related quality of life (as measured by EQ-5D-5 L) [22].

The definitions for secondary outcomes are consistent with international guidelines [23]. Re-ulceration is defined as healing of index ulcer followed by subsequent ulceration with loss of epithelialisation at the same location. A minor amputation is an amputation below the ankle including toe, metatarsal-phalangeal and midfoot amputations. A major amputation is an amputation above the ankle including below knee and above knee amputations. New onset infection includes infections that have commenced during the preceding 2 weeks, including existing ulcers that have never previously been infected.

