## Statistical considerations

### Primary and secondary outcomes

All analyses will be conducted according to the intention-to-treat principle. Baseline characteristics will be compared by treatment group. Effects of treatment on the primary study endpoint (complete healing of the index ulcer at 6 months) will be estimated with the use of unadjusted logistic regression with last observation carried forward for those lost to follow-up. All *P*-values will be two-sided and *P*-values less than 0.05 will be considered to indicate statistical significance. Multiple logistic regression will be applied to adjust for prognostic factors such as vascular insufficiency and site of DFU (fore-, mid- or hind foot) which are strongly correlated with the outcome (*r* ≥ 0.3) [25, 26]. Binary secondary outcomes at 12 months will be analysed similarly. For continuous secondary outcomes, change score analysis that determines treatment effect based on the difference between baseline and post treatment score (basic adjustment) will be undertaken. Multiple linear regression adjusting for i) the baseline value of the outcome variable in the model (model 1), and ii) model 1 + adjustment for prognostic baseline factors (model 2) will be undertaken. Data will be analysed using IBM SPSS Statistics 25.

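### The SAE and AE form triggers are closed lists with no open item, so an unlisted harm of the harvest or cell application need not reach the DSMB

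*Protocol article*

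**What the plan says.** The Adverse events section states that "adverse events (AE) will be pre-specified and reported to the Data Safety and Monitoring Board", and that this is done "in accordance with NHMRC position statement of monitoring and reporting of clinical trials". It then fixes the triggers item by item.

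- "A severe adverse event (SAE) form will be reported promptly to the DSMB if any of the following occurs": three items follow. They are any death, a major amputation on the index leg within 12 months of enrolment, and a harvest-site infection serious enough for admission, surgery or intravenous treatment.
- "An AE form will be reported if any of the following occurs": four items follow. They are readmission because the index ulcer is infected or worse, a minor amputation on the index foot that is not related to the index ulcer, a milder harvest-site infection, and a harvest site that still needs a dressing at the 4-week visit or later.

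The Secondary outcomes section includes "iv) major adverse events, v) any minor or major lower limb amputation, vi) all-cause mortality" and "x) readmission to hospital", the last without restriction on cause. For the comparison, the Statistical considerations section says: "Binary secondary outcomes at 12 months will be analysed similarly", that is, by logistic regression as for the primary outcome. The Rationale says that "no randomised trial of this product has been completed or is currently planned".

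**The concern.** Both lists consist of harms foreseen in advance, and neither ends with an item for any other event. The intervention adds three things that standard care lacks: a skin harvest from the thigh, a trypsin-based cell preparation, and a dressing left undisturbed on the wound for at least 5 days. For the harvest, only infection and slow healing are listed. For the preparation and dressing, nothing is listed except what shows up as readmission for the index ulcer.

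By the article's own account, randomised evidence on this product does not yet exist, so harms that nobody has listed are part of what the trial should be able to detect. If staff follow the lists as printed, the DSMB may not hear promptly of such a harm, and the final report may have no row for it.

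**Working it through.** The point is textual, so the check sets the form triggers beside the outcomes that are compared between arms.

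| Event | Form required by the lists | Compared between arms |
|---|---|---|
| Death | SAE | Yes, as mortality |
| Major amputation, index leg | SAE | Yes, as amputation |
| Minor amputation because of the index ulcer | None, unless it comes with readmission for infection or deterioration of that ulcer | Yes, as amputation |
| Readmission for a cause other than the index ulcer or a harvest-site infection | None | Yes, as readmission, cause not identified |
| Harvest bleeding, or reaction to the preparation or dressing, with readmission | None, unless it also meets a listed item | Yes, as readmission, cause not identified |
| The same, without readmission | None, unless it also meets a listed item | Only if counted as a major adverse event, which is undefined |

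Two things follow from the table.

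1. The form triggers are narrower than the secondary outcomes. Rows three to five are compared at the end of the trial but do not require notice to the DSMB when they happen.
2. The last row depends wholly on how major adverse events is read. The article neither ties that term to the listed triggers nor opens it to other events.

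The plan gives no figure on this point that could be reproduced. An illustration shows whether an unlisted harm could occur in a trial of this size.

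- Inputs: the recruitment target of 150 (Study design). Allocation of 1:1 is an assumption, because the article gives block sizes but no ratio. That makes 150 / 2 = 75 treated patients. The true risks are hypothetical.
- Formula: P(at least one case) = 1 − (1 − p)^n.
- p = 1%: 1 − 0.99^75 = 0.529.
- p = 2%: 1 − 0.98^75 = 0.780.
- p = 5%: 1 − 0.95^75 = 0.979.
- With the 136 patients of the sample size calculation, n = 136 / 2 = 68, and the values are 0.495, 0.747 and 0.969.

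These are probabilities that a harm occurs. They are not probabilities that it is missed.

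**The case against.** A reader might infer from the closed lists that an unexpected serious harm would be neither reported nor compared, and that no harm short of death would reach the DSMB or the results. The documents do not support this. Readmission from any cause, any lower limb amputation and mortality are secondary outcomes, and binary ones are compared by arm. Major amputation of the index leg and readmission for a worsening index ulcer also trigger forms. The Health economic analyses section collects hospital stay and theatre visits, so hospital-treated events leave some trace.

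Three further arguments can be made.

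- *The reporting standard.* Reporting is bound to a national position statement, which may require more than the lists. Its content is not in the documents, so it neither closes the gap nor proves it. If it is wider than the lists, the two need to be reconciled.
- *The condensed article.* An article may leave case report form items and safety tables to the full protocol. That would answer a complaint about silence. Here the article fixes the triggers one by one, with definitions, and the gap lies in what it fixes. It remains true that the lists say when a form is due and do not say that no other form may be sent.
- *Proportionality.* The product is autologous and not systemic, the harvest is about 2 cm², and the article reports successful use in scars, burns and other ulcers. Targeted collection is therefore a defensible choice for expected harms. It does not cover unexpected ones.

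The first paragraph stands and limits the point. What remains is that a comparison at 12 months is not prompt notice to the DSMB, all-cause readmission does not identify a treatment-related cause, and a harm managed without readmission may be counted nowhere.

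**Conclusion.** The point holds in a limited form. The SAE and AE triggers are closed lists of three and four events, and major adverse events is undefined. Under these lists, an unlisted harm of the harvest or cell application requires no form to the DSMB. Nor does a minor amputation due to the index ulcer, unless it comes with a readmission for infection or deterioration of that ulcer. Comparison between arms is assured only for readmission, amputation and death.

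The size of the gap cannot be computed from the documents. The 53%, 78% and 98% rest on 1:1 allocation and on assumed risks of 1%, 2% and 5%. They show only that an unlisted harm could plausibly occur among about 75 treated patients. The conclusion rests on the lists as printed; a fuller protocol or the cited standard may already contain an open item. The change is worth making because events not recorded at the time are hard to recover after follow-up ends.

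**What to change.** 1. Add to the SAE list an item for any other serious event, and to the AE list an item for any other event judged possibly related to the harvest or the application.
2. Ask about both in both arms at the scheduled visits and the fortnightly calls that are already planned. Use the same open question in each arm and judge relatedness afterwards. Only treated patients can have a harvest-related event, and the trial is open label, so uneven questioning would distort the comparison.
3. Define major adverse events so that it includes the open SAE item.
4. Tabulate listed and unlisted events by arm.
5. Check both lists against the reporting standard that the section cites, and reconcile any difference.

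The cost is a line in each list, a definition and a free-text item on existing forms. The downside is more forms in a patient group that uses hospital often, most of them for events unrelated to the treatment.
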